### Recruitment

The recruitment started in April 2012. The 124 breast hypertrophy patients will be selected from the plastic surgery clinics of the hospital of the Universidade do Vale do Sapucaí, where these procedures are routinely performed and followed, ensuring patient compliance. All surgeries will be performed in the operating room of this hospital.

### Allocation – randomization

Patients will be randomly allocated into the study groups based on a random sequence generated by Bioestat 5.0 software (Instituto Mamirauá, Belém, Brazil). Patients in the experimental group (*n* = 62) will receive 500 mg cephalexin capsules, while patients in the placebo group (*n* = 62) will receive placebo capsules, that are identical in appearance to the antibiotic capsules. The antibiotic and placebo capsules were provided in identical packages containing the exact number of capsules for each patient.

### Allocation – concealment mechanism

A researcher, who will not participate in the care of patients, numbered the packages from 1 to 124 as per the randomly generated sequence. At the time of hospital discharge, each patient will receive a serial number and the corresponding numbered package containing the capsules that she will take.

### Allocation – implementation

Only one of the researchers will have access to the random sequence. He will not be responsible for recruiting patients, performing surgical procedures, distributing the packages, or performing postoperative follow-up, ensuring allocation concealment.

### Blinding

The surgery team, the assistant surgeon who instructs patients regarding the capsule intake and the surgeon who evaluates the SSIs are blinded to the allocation group. In addition, the patients are not informed about the contents of their prescribed capsules.

The first assessment regarding SSI is after 7 days. However, patients are instructed to contact the assistant surgeon in case of pain, fever or any other intercurrence before this first assessment. If the assistant surgeon diagnoses a SSI during the use of the antibiotic or placebo, the appropriate antibiotic treatment is immediately established and the use of the study capsules is suspended, without unblinding. Table 1 presents the schedule of the trial.

**Table 1 Tab1:** Schedule of enrolment, interventions, and assessments for “Antibiotic prophylaxis in reduction mammaplasty: a randomized controlled trial”

	Study period				
	Enrolment	Allocation	Post-allocation		Close-out
Timepoint	Apr/2012–Dec/2016	Jan/2015–Jan/2017	Jan/2015–Jan/2017	Feb/2015–Feb/2017	Mar/2017
Enrolment:					
Eligibility screen	X				
Informed consent	X	X			
Allocation		X			
Interventions:					
Reduction mammaplasty		X			
[Antibiotic or placebo prescription]			X	X	
Assessments:					
[Eligibility criteria]	X	X			
[SSI assessment ]			-	X	X

### Data collection methods

Researchers will collect demographic data using a standardized form for each patient during their first medical appointment. Data from weekly postoperative appointments evaluating SSIs will also be collected using a standardized form.

### Data management

All data collected during the study will be entered into a unique spreadsheet, respecting the allocation and blinding. At the end of the study, after the last patient has been recruited, operated on and completed follow-up, the allocation group of each patient will be revealed and separate spreadsheets will be prepared for the data from experimental and placebo groups. The data from these two spreadsheets will be then compared with each other. Each patient will be identified only by a protocol number (the number of her package), to protect her privacy.

## Statistical methods

### Statistical methods – outcomes

The data will be entered into the statistical software Bioestat, version 5.0 (Instituto Mamirauá, Belém, Brazil). Descriptive statistics will be used to evaluate numerical variables, with calculation of the median, mean and standard deviation. The Mann-Whitney test will be used to compare the groups in age, BMI, duration of surgery, and weight of resected breast tissue.

The chi-square test or Fisher’s exact test will be used to compare the occurrence of SSIs among the groups. Those tests will be also used to study associations between the occurrence of infection and age, BMI, duration of the surgery, and weight of resected breast tissue in each group. For these variables, the values for each group will be divided into below the median and above the median.

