**Methods:**

This is a double-blind randomized clinical trial with 124 breast hypertrophy patients allocated to two treatment groups: antibiotic (*n* = 62) and placebo (*n* = 62). All patients will undergo reduction mammoplasty, performed by the same surgical team. The surgeons will raise the nipple-areola complex by the superomedial pedicle technique. The patients will receive antibiotics intravenously during anesthetic induction and every 6 hours thereafter during their 24-hour hospital stay. During discharge from the hospital, each patient will receive a numbered package containing either cephalexin or placebo capsules and will be directed to take one capsule every 6 hours for 7 days. Neither the surgery team nor the patients will know the contents of the capsules. Patients will be monitored for the occurrence of SSI once weekly during the first 30 days following hospital discharge by a single surgeon who is blinded to their treatment group. SSI will be evaluated based on the definition adopted by the Centers for Disease Control and Prevention.

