The impact of infection on wound healing after breast reduction surgery ranges from minor complications, such as marginal necrosis, which is common at the junction of the inverted “T” incision, to major infections that require surgical intervention [23]. Many surgeons prefer to administer antibiotics, believing that it will reduce the incidence of these problems; however, previous studies suggest that antibiotic prophylaxis fails to reduce the rates of infection in clean surgeries, such as breast reduction [7, 14, 23–26].

Among studies conducted in different countries (United Kingdom, Ireland, Israel, and the United States), there was a tendency to prescribe prophylactic antibiotics beyond the intra- and postoperative periods (24 hours) of breast reduction, ranging up to 14 days. Cephalosporins were the most frequently prescribed, with the exception of the UK, which mentioned the use of amoxicillin/clavulanic acid in 70% of cases [9, 19, 21–23, 27–31].

Veiga-Filho et al. [32] compared SSI rates in patients receiving cephalexin for 7 days after hospital discharge (24 hours after breast reduction surgery) to patients who did not receive antibiotics. They observed significantly higher SSI incidence rates in the control group compared with the experimental group receiving antibiotics (14% vs. 2%, respectively; *p* = 0.03). They also observed that the incidence of SSIs was greater in older patients and in patients with a greater resected breast tissue mass (*p* = 0.02; *p* = 0.04, respectively) [32].

Reduction mammaplasty is an effective procedure that improves the quality of life for women with breast hypertrophy and is one of the most common plastic surgery procedures [33–36]. Prevention of SSIs is extremely important, because infection may compromise the outcome of the procedure, and increase the length of stay and costs of hospitalization [37].

This study was designed to address the lack of consensus on the role of antibiotics in breast reduction surgery. Despite the absence of solid evidence, the use of antibiotics following reduction mammaplasty is widespread, and a previous nonrandomized trial demonstrated higher SSI rates when no antibiotics were used. Thus, this trial was designed to compare the effectiveness of antibiotics prophylaxis for 24 hours with the extended use of antibiotics for 7 additional days.

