### Outcome measures

The CDC considers an infection to be an SSI when it appears to be related to the surgical procedure and presents within 30 days of the operation. If implants are inserted during the surgery, the time frame is extended up to a year after the surgery [1]. CDC classifies SSI into three categories, superficial incisional, deep incisional or organ/space SSI. In the present study, as none of the patients received an implant, requiring a delayed assessment, patients will be monitored for the occurrence of infection once a week for the first 30 days following surgery as assessed by a single surgeon, who is a senior plastic surgeon, with extensive experience in breast surgery. This surgeon will diagnose the presence or absence of SSI, thus dichotomizing the outcome as development of SSI (Yes/No). In case of a SSI, it will be classified according to CDC’s criteria, by the same surgeon [1].

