### Sample size

The experimental and control groups were designed for 62 patients each to ensure a significance level of 5% and power of 80%. This was calculated based on the proportions observed in a previous study with and without the use of antibiotics after breast reduction [32].

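### The SSI comparison is left as chi-square or Fisher with no rule, sidedness or correction; naming Boschloo's two-sided exact test would settle it and give about 10 points more power than Fisher at the design rates

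*Protocol article*

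**What the plan says.** Under Statistical methods – outcomes, the protocol article states: "The chi-square test or Fisher’s exact test will be used to compare the occurrence of SSIs among the groups". It does not say when each test applies, whether the test is one- or two-sided, or whether chi-square carries a continuity correction.

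Under Sample size: "The experimental and control groups were designed for 62 patients each to ensure a significance level of 5% and power of 80" per cent. The basis is given as: "This was calculated based on the proportions observed in a previous study with and without the use of antibiotics after breast reduction". No test or sidedness is named there either. The Background reports the earlier study's SSI rates, control against antibiotic, as "14% vs. 2%, respectively".

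Under Data management, after the last patient completes follow-up, "the allocation group of each patient will be revealed and separate spreadsheets will be prepared", and the groups are then compared. Trial status reports no SSI within 30 days among the 90 patients operated on by January 2016.

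**The concern.** The outcome is binary, the arms are small and few events are expected. In that setting chi-square and Fisher are not interchangeable. Uncorrected chi-square runs close to its nominal level, while Fisher runs well below it, so they split on tables near the 5% boundary. A plan that names both, with nothing to separate them, does not fix the verdict on those tables. Its power also cannot be stated, because that depends on which test is meant.

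A better choice than either is available. An unconditional exact test recovers much of the power Fisher gives up and still guarantees the error rate.

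**Working it through.** **Inputs.** 62 per arm, 5% significance and 80% power (Sample size); 14% and 2% (Background, the earlier study cited under Sample size); binary SSI outcome (Outcome measures). Sidedness and correction are not stated.

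**1. The plan's own figure.** With pooled rate (0.14 + 0.02)/2 = 0.08:

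n = [z(α)·√(2·0.08·0.92) + z(β)·√(0.14·0.86 + 0.02·0.98)]² / 0.12²

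- One-sided 5%: [1.645·0.3837 + 0.842·0.3742]² / 0.0144 ≈ 62.2, so 63 (61 with unpooled variance).
- Two-sided 5%: [1.960·0.3837 + 0.842·0.3742]² / 0.0144 ≈ 79.1, so 80 (77 unpooled).

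So 62 per arm reproduces, within rounding, only as a one-sided 5% calculation without correction. Normal-approximation power at 62 per arm is 79.9% one-sided and 69.7% two-sided.

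**2. Where the tests split (62 against 62, two-sided).** Worked for 4-0:

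- Uncorrected chi-square: 124·(4·62 − 0·58)² / (62·62·4·120) = 4.13, p = 0.042.
- Yates: 124·(248 − 62)² / (62·62·4·120) = 2.33, p = 0.127.
- Fisher: 2·(62·61·60·59)/(124·123·122·121) = 0.119.

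| SSIs | Chi-square, uncorrected | Yates | Fisher | Smallest expected count |
|---|---|---|---|---|
| 4-0 | 0.042 | 0.127 | 0.119 | 2.0 |
| 5-0 | 0.022 | 0.068 | 0.057 | 2.5 |
| 7-1 | 0.028 | 0.068 | 0.062 | 4.0 |
| 8-2 | 0.048 | 0.099 | 0.095 | 5.0 |
| 9-2 | 0.027 | 0.058 | 0.054 | 5.5 |

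Summing binomial probabilities over all tables at 14%/2%, uncorrected chi-square and Fisher disagree with probability 15.3%. Yates and Fisher do not disagree on any table with non-negligible probability.

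The expected SSI count per arm is (8.68 + 1.24)/2 = 4.96, next to the customary threshold of 5. The chance that the smallest expected count falls below 5 is 46%.

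**3. Exact power and size.** Boschloo's test uses the two-sided Fisher p-value as its statistic and rejects at the largest cut-off that keeps the maximum size over all common SSI rates at or below 5%. Here that cut-off is 0.0692. Its rejection region contains Fisher's, so it cannot be less powerful.

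| Two-sided test at 5% | Power at 14%/2% | Type I error |
|---|---|---|
| Fisher (Yates the same) | 59.6% | 1.9% at an 8% rate; 3.8% at worst |
| Fisher if smallest expected count is below 5, otherwise uncorrected chi-square | 67.4% | 4.0% at an 8% rate |
| Boschloo | 69.5% | 4.99% at worst |
| Uncorrected chi-square | 74.9% | 5.05% at an 8% rate; about 5.1% or less up to 15%; 5.9% at worst |

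The worst case for Fisher and for uncorrected chi-square is at a common SSI rate of 50%.

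Against the expected-count rule, Boschloo has 41% against 34% power at 10%/2% and 39% against 22% at 6.6%/0% (both illustrative rates).

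**4. What is still attainable.** After 0 SSIs in 90 patients, 124 − 90 = 34 remain. If all further SSIs fall in one arm, significance needs 4 by uncorrected chi-square, 5 by Boschloo and 6 by Fisher. Assuming the 34 split 17/17, the chance that uncorrected chi-square and Fisher disagree is 0.2% at 3%/3%, 0.7% at 5%/1% and 2.2% at 6.6%/0%. Boschloo's gain over Fisher in that last case is 0.3 points.

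**The case against.** The strongest reply is that naming both tests is ordinary shorthand for the expected-count rule, which a condensed article may leave to an analysis plan not shown. That stands: the missing rule on its own would only be missing detail. With equal arms the smallest expected count is half the total number of SSIs, so the customary rule can be applied to the pooled count before allocation is revealed. It sends 4-0, 5-0 and 7-1 to Fisher and 8-2 and 9-2 to chi-square, one verdict each.

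A reader might infer that the test will be picked after seeing which p-value is smaller, and that this inflates type I error. The documents do not support that. Data management describes when allocation is revealed, not how a test is chosen. Even always taking the smaller p-value keeps the error at about 5.1% or less for SSI rates up to 15%.

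The split also depends on chi-square being uncorrected; with Yates it vanishes. And 0 SSIs in 90 patients has probability (0.86·0.98)^45 ≈ 0.0005 at the design rates (assuming 45 per arm), so power at 14%/2% says little about what this trial will now see. Both qualifications stand. What remains is that a better test is available at little cost and the plan's wording does not select it.

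**Conclusion.** The point holds as a choice of method that is fixed badly. The wording admits at least three procedures (Fisher or Yates, the expected-count rule, uncorrected chi-square) whose exact two-sided power at 14%/2% runs from 59.6% to 74.9%. Boschloo improves on Fisher by 69.5 − 59.6 = 9.9 points and on the expected-count rule by 69.5 − 67.4 = 2.1 points, with error held at or below 5% at every SSI rate.

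Two stronger readings should be avoided. The roughly 10 points is Boschloo against Fisher, not the gap between the two named tests, which is 74.9 − 59.6 = 15.3 points. Nor do the named tests conflict on most tables: disagreement is 15.3% at the design rates and far rarer given the results so far.

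The figures assume 62 analysed per arm, a two-sided 5% level and, for the disagreement, an uncorrected chi-square. The practical effect in this trial is likely small.

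**What to change.** Before allocation is revealed, name one primary test for SSI: Boschloo's unconditional exact test, two-sided at 5%, whatever the cell counts. State the power for that test: 69.5% at 62 per arm under 14%/2%, rather than 80%. Fixing Fisher instead would remove the ambiguity but accept the lower power, so it is not the preferred alternative.

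The cost is a sentence or two through the protocol's amendment procedure. The downside is that software other than Bioestat 5.0 may be needed; free packages exist.

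### Testing infection against four continuous variables by median split within each arm wastes power in a secondary analysis; keeping them continuous and combining the arms costs only wording (minor)

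*Protocol article*

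**What the plan says.** Under Statistical methods – outcomes, the protocol article names the chi-square or Fisher's exact test for the between-arm comparison of SSI. It then extends the same tests to risk factors: "Those tests will be also used to study associations between the occurrence of infection and age, BMI, duration of the surgery". Resected weight is the fourth variable on that list, and the tests are to be run within each arm separately. The four variables are dichotomised first: "For these variables, the values for each group will be divided into below the median and above the median". The most natural reading is that each arm is cut at its own median, although one overall median is not strictly excluded. Four variables in two arms make eight tests. No combined, continuous or arm-adjusted analysis of these factors is described.

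The same section already uses a rank test on the undivided values for another purpose: "The Mann-Whitney test will be used to compare the groups in age, BMI, duration of surgery, and weight of resected breast tissue".

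The Background reports from the previous nonrandomized study that "the incidence of SSIs was greater in older patients and in patients with a greater resected breast tissue mass". Under Sample size, "The experimental and control groups were designed for 62 patients each", and the rates come from that study: "This was calculated based on the proportions observed in a previous study with and without the use of antibiotics after breast reduction". The Background gives them as 14% without and 2% with antibiotics. Trial status reports no infection within 30 days among the 90 patients operated on by January 2016.

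**The concern.** Cutting a continuous variable at its median discards the ordering within each half. Testing each arm alone also divides an already small number of infections. Both choices are fixed in the text, so this is a stated method and not a detail left to another document.

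The stake is how the results will be read. Age and resected weight were reported as risk factors in the study that supplied the planning rates. A non-significant result from a test with little chance of detecting an association could be taken as evidence against one. If each arm has its own cut-point, the upper half also need not cover the same values in the two arms, so the two sets of results are not strictly comparable.

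**Working it through.** **Inputs.** From the article: 62 patients per arm; planning rates 14% (placebo) and 2% (antibiotic); no SSI in the first 90 of 124. Assumed, because the article gives no effect size: a normally distributed covariate and an odds ratio (OR) of 1.5 to 3 per SD. Tests are two-sided at 5%.

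**The plan's own figure.** The usual two-proportion formula with 14% and 2% and 80% power is n = [z_α√(2 × 0.08 × 0.92) + z_β√(0.14 × 0.86 + 0.02 × 0.98)]² / 0.12². One-sided, this is (1.645 × 0.3837 + 0.8416 × 0.3742)² / 0.0144 = 62.1. Two-sided, it gives 80 after rounding up. So 62 does follow from 14% and 2%, as a one-sided calculation, and these are the rates to use below.

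**Expected events.** Antibiotic arm: 62 × 0.02 = 1.24. Placebo arm: 62 × 0.14 = 8.68, or 4.34 per half. That is below the usual threshold of 5, so Fisher is the likelier test.

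**Antibiotic arm: events needed.** Take a 31/31 split with all k events in one half, the most extreme result possible.
- Fisher: p = 2·C(31,k)/C(62,k). For k = 4, 5, 6 this is 0.113, 0.0525 and 0.024, so at least 6 events are needed.
- Uncorrected chi-square: X² = 62k/(62 − k). For k = 3 it is 186/59 = 3.15; for k = 4 it is 248/58 = 4.28, against a critical value of 3.84. At least 4 events are needed.
- Binomial(62, 0.02): P(6 or more) = 0.15%, P(4 or more) = 3.6%, P(none) = 0.98^62 = 28.6%.

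These event counts are necessary but not sufficient, because at the minimum count every event must fall in the same half. None of this depends on an assumed OR.

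**Placebo arm.** With 9 events, Fisher needs an 8:1 split (p = 0.026) or 9:0; 7:2 gives p = 0.15.

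**Simulated power** (10,000 replicates, logistic model; continuous tests are score tests):

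| OR per SD | Placebo arm, split + Fisher | Placebo arm, split + chi-square | Placebo arm, continuous | Antibiotic arm, continuous | Both arms, continuous, stratified by arm |
|---|---|---|---|---|---|
| 1.5 | 6% | 14% | 19% | 6% | 22% |
| 2 | 16% | 29% | 42% | 10% | 48% |
| 2.5 | 26% | 43% | 62% | 15% | 70% |
| 3 | 35% | 55% | 76% | 19% | 82% |

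A Mann-Whitney test in the placebo arm at OR 2 gives about 40%, in line with the 42% here. The planned split in the antibiotic arm has 0.0% power with Fisher and 0.7% to 1.9% with chi-square.

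**Cost of the split in the placebo arm at OR 2.** With chi-square, (42.0 − 29.4)/42.0 = 30% of the power is lost. With Fisher, (42.0 − 15.5)/42.0 = 63%. The difference between the two is Fisher's conservatism.

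**Effect of the events so far.** The last column assumes about 10 events (124 × 0.08). With none in 90, even 8% among the remaining 34 gives 34 × 0.08 = 2.7 expected events. Simulated that way, a continuous test on all patients has about 15% power at OR 2 and about 30% at OR 3.

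**The case against.** The strongest reply is that the split is not the main obstacle. A reader might infer that median splitting makes the antibiotic-arm analysis impossible. The figures do not support that. At the planned 2% a significant result is very improbable but not excluded, and the cause is about 1.2 expected events: a continuous test confined to that arm has only 6% to 19% power. This part of the reply stands.

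A reader might also infer that the split discards most of the power. That holds only with Fisher and under assumed odds ratios. With uncorrected chi-square, which the plan also names, the loss within the placebo arm is about a quarter to 30%.

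On the cut-points, the article plans no comparison of associations between arms. All four variables are fixed before packages are handed out at discharge, so two arm-specific medians would differ only by chance, typically by about 0.15 SD for a normal variable. The objection is right in principle but small. Where a value equal to the median goes is a detail that a condensed article may leave out.

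Finally, confirming earlier risk factors is not the stated objective, and with no SSI in 90 patients the alternative may recover little. Both are true. They lower the importance of the point but do not defend the planned method, which gives up power for no stated benefit.

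**Conclusion.** The point holds as a minor one. The fixed analysis is weaker than an equally simple alternative. At the planning rates and an assumed OR of 2 per SD, placebo-arm power is about 16% (Fisher) or 29% (chi-square), against about 40% for a continuous test in the same arm and 48% with both arms combined. In the antibiotic arm, significance is practically unattainable at 2%, mainly because that arm is tested alone. The antibiotic-arm event thresholds rest only on the article's figures; the power figures rest on the assumed normal covariate and odds ratios.

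It would be wrong to read the combined-arm powers of 48% and 82% (OR 2 and 3) as what the change would deliver in this trial. They require about 10 infections, and the article reports none among the first 90 patients. Actual power will be far lower, and if no infection occurs neither the planned analysis nor any replacement can estimate an association. The primary comparison of SSI between arms is untouched.

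**What to change.** Reword the risk-factor part of Statistical methods – outcomes as follows:
- Keep age, BMI, duration of surgery and resected weight continuous.
- Analyse both arms together, stratified or adjusted for arm. Firth logistic regression with arm and one covariate at a time suits sparse events. A Mann-Whitney comparison of patients with and without SSI, stratified by arm, is a simpler option built on a test the plan already uses.
- Report estimates with 95% confidence intervals, labelled exploratory. State that no association will be estimated if there are no events.
- If a split is still shown for description, use one common cut-point for both arms and say on which side a value equal to it falls.

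This changes analysis wording only. It needs no new data or patients, and the variables are already to be collected.
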